## Abstract

**Background:**

Subthalamic deep brain stimulation (STN-DBS) effectively treats motor symptoms in appropriately selected patients with Parkinson’s disease, but individual responses vary. Despite modern directional leads allowing more precise stimulation, optimal contact selection strategies have not yet been standardized. This study compares a standardized imaging-guided contact selection protocol to conventional clinical programming.

**Methods:**

We designed a monocentric, randomized, double-blind crossover trial enrolling 30 people with Parkinson’s disease with bilateral directional STN-DBS. Participants will undergo both programming approaches: standardized imaging-guided contact selection targeting the dorsolateral STN and conventional contact selection through clinical test stimulations. Each configuration will be applied for 1 week. The primary outcome is patient preference after both treatments. Secondary outcomes include motor assessments (MDS-UPDRS III), accelerometric monitoring, and questionnaire-based quality of life measures (e.g., PDQ-39).

**Discussion:**

This study addresses a critical gap in standardization of imaging-guided DBS programming. By using patient preference as the primary outcome, we aim to capture clinically meaningful differences that may not be detected with traditional motor scales. The crossover design balances statistical power with clinical feasibility in specialized care settings.

**Trial registration:**

Deutsches Register für Klinische Studien DRKS00034229. Registered on May 27, 2024.

## Administrative information

Note: the numbers in curly brackets in this protocol refer to SPIRIT checklist item numbers. The order of the items has been modified to group similar items (see http://www.equator-network.org/reporting-guidelines/spirit-2013-statement-defining-standard-protocol-items-for-clinical-trials/).

## Introduction

### Background and rationale {6a}

Subthalamic deep brain stimulation (DBS) is a well-established neuromodulation therapy used to alleviate the motor symptoms of Parkinson’s disease (PD) [1, 2]. It effectively reduces motor fluctuations and decreases the required dosages of dopaminergic medication, maintaining these benefits well beyond the immediate postoperative phase [3]. However, individual treatment responses remain variable, highlighting the need for further optimization to enable consistent clinical outcomes across a broader patient population [4].

A critical prerequisite for achieving optimal stimulation effects is the precise placement of the electric field [5, 6]. Extensive research has established that stimulation of the posterodorsal aspect of the subthalamic nucleus (STN) is most effective in reducing akinetic-rigid symptoms with minimal side effects [7–10]. To further enhance the precision of stimulation beyond the initial implantation, modern DBS leads are equipped with multiple segmented contacts [11, 12]. These allow for vertical and horizontal current steering, thereby facilitating more targeted stimulation [13].

Traditionally, optimal stimulation contacts are identified through a monopolar review, i.e., multiple test stimulations conducted during a comprehensive clinical examination by a DBS expert [14, 15]. While generally deemed effective, this process is cumbersome, subjective, and time-consuming and has become increasingly more complex with the modern DBS lead design [16, 17].

In recent years, several software solutions have been introduced that enable visualization of the individual lead position in relation to the target brain structures [18, 19]. Multiple studies have demonstrated that expert clinicians can determine effective stimulation contacts using this imaging data in a more time-efficient manner compared to conventional approaches [20–23]. However, the optimal strategy for imaging-guided DBS programming remains to be established. Comparative correlation analyses suggest that even minor differences in contact selection strategies may significantly impact treatment outcomes [24].

So far, efforts to standardize imaging-guided DBS programming have been limited. Prior investigations have refrained from specifying the exact algorithms or decision-making processes used for contact selection based on visual information, thereby limiting reproducibility and generalizability. To address this gap, we designed a randomized double-blind crossover trial to compare a standardized protocol for imaging-guided contact selection to conventional DBS programming.

### Objectives {7}

Does standardized imaging-guided contact selection facilitate equal symptom control compared to conventional contact selection for STN-DBS in PD?

## Methods: participants, interventions, and outcomes

### Study setting {9}

This study will be executed as a monocentric study (University Hospital Cologne, Cologne, Germany).

### Eligibility criteria {10}

Inclusion criteria:Clinically confirmed diagnosis of Parkinson’s disease according to current MDS criteria [27]Implanted DBS system with bilateral directional leads for at least 10 weeksAvailability of high-resolution cranial preoperative MRI and postoperative CT from routine clinical imagingStable Parkinson’s disease-specific medication regimen for at least 2 weeksAge over 18 years

Exclusion criteria:Debilitating postural instabilityCognitive impairment meeting diagnostic criteria for dementiaVestibular or orthopedic comorbidities with significant impact on daily functioningDopamine dysregulation syndromeInability or unwillingness to reliably operate the DBS system’s remote control

### Who will take informed consent? {26a}

Informed consent will be obtained from all potential participants both in written and oral form by study physicians prior to enrollment in the trial.

### Additional consent provisions for collection and use of participant data and biological specimens {26b}

No biological specimens will be collected in this study. Participant data will be collected according to established guidelines, with no provisions for use in ancillary studies. The informed consent process addresses only the data collection and use for the current trial.

## Interventions

### Explanation for the choice of comparators {6b}

The two DBS programming approaches were selected for comparison based on their clinical relevance and potential impact on patient care. Conventional clinical contact selection through test stimulations represents the current standard of care in most DBS centers worldwide and has established efficacy. However, this approach is time-consuming, requires specialized expertise, and may be subject to inter-examiner variability [20, 21].

Standardized imaging-guided contact selection has emerged as a potentially more efficient alternative that might provide more consistent outcomes across centers [23]. Our specific standardized protocol targeting the dorsolateral STN is based on our clinical experience with imaging-guided DBS programming and previous research showing this approach’s association with optimal motor improvement [24].

### Intervention description {11a}

The study intervention will be a DBS program with a contact selection based on individual imaging. The required imaging is acquired during our clinical routine: preoperative isometric (1.0 mm^3^ voxel size) T1- and T2-weighted MRI (3 T Ingenia, Achieva, 1.5 T Ingenia, Philips Healthcare, The Netherlands) and a postoperative high-resolution CT scan (IQon Spectral CT, iCT 256, Brilliance 256, Philips Healthcare, The Netherlands). Imaging will be assessed with a proprietary software (Brainlab Elements GUIDE XT, Brainlab, Munich, Germany). After automated fusion of the available images, three nuclei will be segmented using the integrated segmentation function (nucleus ruber, substantia nigra, subthalamic nucleus). The dorsal, lateral, and medial borders of the STN are refined based on the T2 hypointensity. The lead positions will be determined using the automated lead detection algorithm. Lead orientations will either be determined via the automatic lead orientation detection algorithm or assessed visually, if necessary. Standardized imaging-guided contact selections will be determined with the 3D visualization of a representative VTA (volume of tissue activated; 2 mA, 60 µs, 130 Hz), which is positioned following a predetermined strategy [24]:If a lead is positioned in the visual center of the posterior third of the STN, omnidirectional settings are selected. Otherwise, the maximal directional focus is applied and faced toward the posterior third of the STN.Contact levels close to the dorsal border of the STN are selected to align the dorsal border of the VTA with the dorsal border of the STN, focusing on the dorsal motor STN. If a ring contact is the closest to the dorsal border of the STN with a lead positioned off-center to the posterior third of the STN, directional contacts on the neighboring level can be used to facilitate directional stimulation at the investigator’s discretion.

The control intervention will be a DBS program with a contact selection determined during a physical examination after overnight cessation of dopaminergic medications with test stimulations by movement disorder experts with extensive experience in DBS treatment. During the examination, the most effective level will be determined; multi-level configurations are permitted at the clinician’s discretion. Directional settings will be selected, when the clinician deems a clinical benefit during test stimulations.

Both DBS programs will apply pulses with 60 µs at 130 Hz. The initial amplitudes are determined based on a subsequent blinded amplitude titration and determined as rigidity threshold + 0.5 mA. Each DBS program will be applied for a week. Study participants will be asked to autonomously titrate the optimal amplitudes during the first 3 days of the respective treatment weeks. During the following 3 days, amplitudes will be kept stable.

### Criteria for discontinuing or modifying allocated interventions {11b}

Adverse events, including stimulation-induced side effects, will be monitored and documented throughout the study duration. Participants retain the right to withdraw from the study at any time without explanation. Should a participant choose to discontinue a treatment week, they may still proceed to the subsequent treatment phase if the aborted week was their first allocation. Assessment of treatment preference will occur regardless of whether participants complete both treatment weeks. To ensure patient safety, each participant will have their established DBS program available as a rescue option accessible via the patient remote.

### Strategies to improve adherence to interventions {11c}

To ensure adherence to the intervention protocols, each participant will receive a detailed schedule of their treatment periods, instructions for indications for amplitude adjustments, and a motor diary to record daily experiences with each DBS program during the stable treatment phase. Study personnel will conduct regular phone check-ins between scheduled visits to monitor protocol adherence and address any concerns. During on-site visits, the research team will verify DBS program settings to confirm participants are receiving the allocated intervention.

### Relevant concomitant care permitted or prohibited during the trial {11d}

Participants will be advised to maintain their regular medication regimen and routine care throughout the trial period. Participants are prohibited from enrolling in other interventional clinical trials during the study period.

### Provisions for post-trial care {30}

Upon trial completion, participants will transition to regular care at our hospital. Any adverse events related to trial participation will be treated according to standard clinical protocols within our institution. Participants are covered by insurance coverage for trial-related injuries or harm.

### Outcomes {12}

The primary outcome will be patient preference between imaging-guided contact selection and clinical contact selection, which will be captured at the end of the second treatment week as a choice between week 1 and week 2. Participants are allowed to refrain from stating a preference. Secondary outcome measures include clinical (MDS-UPDRS III) and objective (accelerometer) motor symptom assessments as well as patient questionnaires (FOG-Q, PDQ-39, MDS-UPDRS I/II/IV, MDS-NMSS) and motor diaries. Additionally, clinical characteristics of the study population including age, disease duration, and current medication, as well as cognitive status (Montreal Cognitive Assessment), will be recorded at baseline.

### Participant timeline {13}

See Fig. 1.

**Fig. 1 Fig1:**
[figure not shown]
Schematic trial timeline including a schedule of enrollment, interventions, and assessments

### Sample size {14}

Our comparative power simulation (Monte Carlo method with 100,000 iterations, *p*(*b*) = 1 − *p*(*a*), *n* = 10:1:100) evaluated four binary outcome tests across Cohen’s *h* effect sizes. Results revealed the Prescott test of equality minimizes false negatives in small cohorts (*n* < 60) compared to McNemar, sign test, and permutation statistics (Fig. 2). This specialized test was developed in 1981 specifically for crossover designs and demonstrates superior robustness against treatment order effects [26].

**Fig. 2 Fig2:**
[figure not shown]
Statistical power by effect and sample size: Monte Carlo simulation with pseudorandomized probabilities for a binary choice (*p*(*b*) = 1 − *p*(*a*)) with four different test statistics. Each panel shows the analysis for probability distributions representing either a small (left), medium (middle), or large (right) treatment effect as defined by Cohen’s *h*. While permutation statistics (red) and the sign test (yellow) lead to more conservative power estimations across the spectrum of sample sizes than Prescott (blue) and McNemar (green) tests, below the sample size of 60 the Prescott test yields the highest power among the compared tests

Based on the simulations within the framework of Cohen’s *h*, we determined that a study with 27 subjects would achieve 80% statistical power at *α* = 0.05 (two-sided) to detect a true preference difference for detecting large, i.e., substantial and clinically significant differences (Fig. 2). In the binary choice scenario of this study, Cohen’s *h* = 0.8 corresponds to a preference distribution of 70% versus 30%. Anticipating a dropout rate of 10%, we plan to recruit 30 subjects. This investigation will be sufficiently powered to detect or exclude large treatment effects. A non-significant result would provide evidence against the presence of a large treatment effect, though smaller clinically relevant differences may remain undetected and would require larger sample sizes to identify.

### Recruitment {15}

Study participants will be recruited from the patient population of the Neurological Department of the University Hospital Cologne. Suitable candidates will be prescreened based on the available medical records. For definitive screening, possible study participants will be reexamined by a study physician to assess inclusion and exclusion criteria.

## Assignment of interventions: allocation

### Sequence generation {16a}

The allocation sequence will be generated through block randomization. Blocks containing six tokens (3 × AB/3 × BA treatment sequences) will be prepared to ensure balanced allocation of treatment order.

### Concealment mechanism {16b}

The allocation sequence will be concealed using prepared envelopes containing the randomized treatment order tokens. The documented treatment order and interventions will be stored securely in sealed envelopes and a password-protected database.

### Implementation {16c}

One designated study team member will determine the treatment order by drawing from the prepared envelopes, establish the imaging-guided contact selection, and handle the programming devices. This team member will enroll participants and assign them to the intervention sequences. The remaining team members will remain blinded to patient anatomy and active treatment throughout the study.

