## Assignment of interventions: blinding

### Who will be blinded {17a}

This study employs a double-blind design. Trial participants, clinical assessors, and all study team members except for one designated programmer will be blinded to the treatment allocation. The designated programmer will determine treatment order, establish the imaging-guided contact selection, and handle the programming devices, while maintaining confidentiality of the allocation. Clinical DBS programming will be conducted by blinded team members who have no access to the treatment allocation information. Motor scales will be assessed based on video documentation to facilitate blinded ratings.

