### Interim analyses {21b}

For interim safety and efficacy evaluation, a formal analysis will be conducted after completion of the third randomization block (18 subjects, representing >50% of enrollment). The trial will be terminated early if either of two predefined stopping criteria are met:i)Statistical significance (*p* < 0.05) of the Prescott test for the primary endpoint indicating a very large treatment effect.ii)Treatment discontinuation exceeding 70% in either study arm indicating a safety signal.

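### The unblinded programmer both enrols participants and draws the order from constant blocks of six, so the order is not reliably concealed from the person who enrols

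*Protocol article*

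**What the plan says.** Implementation {16c} describes a single designated team member who "will determine the treatment order by drawing from the prepared envelopes, establish the imaging-guided contact selection, and handle the programming devices". The next sentence adds enrolment to the same person's duties: "This team member will enroll participants and assign them to the intervention sequences". Who will be blinded {17a} confirms that this person is the one exception to blinding: "all study team members except for one designated programmer will be blinded to the treatment allocation".

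Sequence generation {16a} fixes the block composition: "Blocks containing six tokens (3 × AB/3 × BA treatment sequences) will be prepared to ensure balanced allocation of treatment order". Interim analyses {21b} shows that the block size is constant, because the interim look is placed by block count: "a formal analysis will be conducted after completion of the third randomization block (18 subjects, representing >50% of enrollment". Concealment mechanism {16b} relies on prepared envelopes that hold the order tokens.

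Two other sections bear on who controls entry. Consent {26a} is taken by study physicians before enrolment. Under Recruitment {15}, "possible study participants will be reexamined by a study physician to assess inclusion and exclusion criteria". Neither section says whether that physician is a different person from the programmer.

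**The concern.** Allocation concealment means that whoever decides on the next participant's entry cannot foresee that participant's allocation. Envelopes achieve this only if the person who enrols has not seen what came out of the earlier ones. Here the person who enrols made every earlier draw and can know that each block holds three of each order, so the remaining content of the block follows by subtraction.

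In a crossover only the order is randomised, so foreknowledge cannot decide who gets which programme. It can decide which kind of patient gets which order, through the choice or timing of entry. Three parts of the planned analysis in Statistical methods {20a} need the AB and BA groups to be exchangeable:

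- **The Prescott test** compares stated preferences between the two sequence groups. If patients inclined to favour one week whatever the programme are over-represented in one sequence, their week preference is counted as a programme preference.
- **The pre-test for sequence effects** compares preference rates in AB and BA. Any selection into sequence feeds straight into it.
- **The first-period-only fallback**, triggered at p < 0.10 in that pre-test, turns sequence into the treatment arm. The within-patient protection is then gone, and selection into sequence becomes selection into treatment. (Preference is recorded once, at the end of week 2, so the article leaves open what first-period data would be for the primary outcome. The statement holds for any outcome to which the fallback is applied.)

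**Working it through.** **Inputs**

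- Block: 6 tokens, 3 AB and 3 BA (Sequence generation {16a}).
- Constant size: the third block ends at 18 subjects (Interim analyses {21b}).
- Planned recruitment: 30, from 27 with 10% dropout (Sample size {14}).
- Assumption: the enroller knows the block size and all earlier draws. This follows from the duties in {16c}.

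**The plan's own figures**

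3 blocks × 6 = 18, as stated. 27 / 0.9 = 30, as stated. 30 / 6 = 5 whole blocks.

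**Orders known with certainty before the draw**

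A block has C(6,3) = 20 equally likely orderings. A position is already determined when all remaining tokens are of one kind.

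- 6th position: always determined, probability 1.
- 5th position: the last two tokens are the same, probability 2 × (3/6 × 2/5) = 2/5.
- 4th position: the last three are the same, 2/20 = 1/10.
- 1st to 3rd positions: never determined.

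Sum: 1 + 0.4 + 0.1 = 1.5 of 6, or 25%. Over five blocks: 5 × 1.5 = 7.5 of 30. The last participant of each block, 5 of 30, is always known.

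**Correct guesses when always guessing the order with more tokens left**

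| Position | State before the draw | Probability of a correct guess |
|---|---|---|
| 1 | 3 and 3 left | 1/2 = 0.5 |
| 2 | 3 and 2 left | 3/5 = 0.6 |
| 3 | 2 and 2 left (prob. 3/5), or 3 and 1 left (2/5) | 3/5 × 1/2 + 2/5 × 3/4 = 0.6 |
| 4 | 2 and 1 left (9/10), or 3 and 0 left (1/10) | 9/10 × 2/3 + 1/10 × 1 = 0.7 |
| 5 | 1 and 1 left (3/5), or 2 and 0 left (2/5) | 3/5 × 1/2 + 2/5 × 1 = 0.7 |
| 6 | one token left | 1.0 |

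Sum: 0.5 + 0.6 + 0.6 + 0.7 + 0.7 + 1.0 = 4.1 of 6, or 68.3%. Over five blocks: 5 × 4.1 = 20.5 of 30.

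**With enrolment separated**

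An enroller who has no access to earlier draws knows 0 of 30 orders in advance and guesses 50%, or 15 of 30. The present arrangement therefore gives 20.5 − 15 = 5.5 extra correct guesses.

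**The case against.** The strongest objection is that little harm can follow. Every participant gets both programmes, so bias needs two things together: patients matched to order, knowingly or not, and week preferences that differ by type of patient. The article gives no sign of either, and the figures above measure predictability, not bias in the preference contrast or in type I error. Study physicians take consent and do the definitive screening, and the monitor verifies all eligibility criteria. This stands as a limit on severity. It does not remove the point: eligibility checks do not control when an eligible person enters, and the text never says that those physicians are separate from the programmer.

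A second objection is that an article leaves detail to the full protocol. That would excuse silence on envelope numbering, for example. It does not excuse an arrangement that the article states outright, which is that one person both enrols and draws.

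A reader might also infer three stronger things that the document does not support.

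- **That the envelopes conceal nothing.** On the enumeration, 75% of orders are not certain in advance. Not reliably concealed is the exact description.
- **That the order is drawn before the imaging-guided selection is made.** The sentence in {16c} lists duties. Read as a time sequence, it would put enrolment after programming. What can be said is only that the article fixes no order for these steps.
- **That the programmer could tune the imaging-guided programme by knowing its week.** The discretion in Intervention description {11a} on choosing a neighbouring directional level covers one narrow case, where a ring contact lies nearest the dorsal border and the lead is off-centre. No mechanism links the week to that choice. The programmer knows which programme is the experimental one whatever the order, so concealing the order would not remove any partiality there.

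**Conclusion.** The point holds as a concealment weakness of moderate weight. Enrolment and the draw sit with the one unblinded person, with constant blocks of six. On average 7.5 of 30 orders are known for certain before enrolment and 20.5 of 30 can be guessed correctly, against 0 and 15 under full concealment. These figures assume that 30 participants fill five whole blocks and that the enroller recalls earlier draws and knows the block size.

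The resulting bias is confined to order and cannot be quantified from the article. It can reach the Prescott test and the sequence pre-test, and it matters most if the first-period-only fallback is used. It does not invalidate the trial, but it should be corrected because correction is cheap.

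**What to change.** 1. Amend Implementation {16c} so that a study physician other than the programmer, without access to earlier draws, makes and records the final enrolment decision. Consent and screening already lie with study physicians. If they are in practice separate from the programmer and already decide on entry, correcting the enrolment sentence is enough for this step.
2. Require both contact selections, imaging-guided and clinical, to be recorded before the order is revealed. This is a simple safeguard and does not imply that selections have been influenced.
3. Let the programmer open only the next sequentially numbered envelope, after steps 1 and 2.
4. Keep the block size. Once enrolment is separated, varying it adds little. A change before the interim look would undo its definition as the end of the third block at 18 subjects. A change afterwards leaves 30 − 18 = 12 places, which whole blocks fill only as 6 + 6 or 4 + 4 + 4: a mix of 4 and 6 gives 10 and leaves 2 over.
5. For participants already enrolled, report the limitation and show baseline characteristics by sequence.

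The cost is a small amendment and a reordering of steps among existing staff, with no extra visits or participants. Trial status gives a recruitment start of July 10, 2024 and an anticipated end of March 31, 2026, so the change protects only those still to be enrolled.
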